##### Duration of all symptoms and each symptom

The duration of all symptoms is defined as the number of hours from enrollment to the time that all symptoms completely disappear. Each patient is required to record any change in symptoms in the subject diary. The investigator will assess the duration of all symptoms and each symptom.

##### Change in TUM symptom score

Currently, there is no grading evaluation standard for Uighur medicine. In this trial, the TUM symptom graded score system follows the *Guidelines for clinical research on new drug of chinese medicine* [20] (see Table 1). The primary symptoms are given a graded score (none = 0, mild = 3, moderate = 6, severe = 9) and the secondary symptoms are given a graded score (none = 0, mild = 1, moderate = 2, severe = 3). TUM signs will also be assessed, but not scored. The total score of TUM symptoms (including primary and secondary symptoms) will be summed at baseline (symptom score before treatment) and the fourth day (symptom score after treatment). The sum of all symptom scores is the cumulative TUM symptom score. The change in cumulative TUM symptom score is assessed by the percentage of symptom score reduction (PSSR), which is calculated according to the following formula:$$ \mathrm{PSSR}=\left(\frac{symptom\ score\ before\ treatment- symp\mathrm{t} om\  score\ after\ treatment}{symptom\ score\ before\ treatment}\right)\times 100\% $$

**Table 1 Tab1:** Symptom scoring system and TUM sign

TUM Symptoms	Score			
Primary	0	3	6	9
Fever	None	37.3 °C–37.9 °C	38 °C–38.5 °C	>38.5 °C
Nasal congestion	None	Mild	Moderate	Severe
Nasal discharge	None	Occasionally	Sometimes	Frequently
Sore throat	None	Dry throat with slight pain	Significant with obvious pain when swallowing	Sore and swollen throat with severe pain
Secondary	0	1	2	3
Cough	None	Occasionally in daytime	Occasionally day and night	Frequently day and night
Headache	None	Slight and occasionally	Slight and lasting	Severe and affecting working
Thirsty	None	Dry mouth	Moderate	Severe and drinking plenty of water
Sweating	None	Mild	Moderate	Severe
Sore limbs	None	Slight	Moderate	Severe
Cumulative symptom score	Primary symptom scores + secondary symptom scores			
TUM sign	Unscored			
Tongue body	□Red	□Others:		
Tongue coating	□Thick and yellow	□Others:		
Pulse condition	□Hard and rapid	□Others:		

*TUM* traditional Uighur medicine

Based on the therapeutic effect evaluation system, the improvement of TUM symptoms will be categorized into clinical recovery (PSSR ≥ 70%) and invalid (PSSR < 70%).

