### Inclusion criteria

The inclusion criteria are as follows: (1) meet the diagnosis of common cold according to Western medicine; (2) meet the diagnosis of CCHS according to traditional Uighur medicine; (3) fever and body temperature between 38 and 39 °C; (4) symptom presenting within 24 h; (5) age between 18 and 65 years and (6) voluntarily participate and provide signed informed consent.

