### Diagnostic criteria

Diagnosis of the common cold in Western medicine is established according to the diagnostic criteria for the common cold of acute upper respiratory tract infection of *Internal Medicine, 8*^*th*^*Version* (2013) [18]. The typical clinical symptoms of common cold include sneezing, nasal congestion, nasal discharge, fever and sore throat.

The TUM diagnosis of CCHS is based on the Clinical research guidelines for treatment of common cold with new Uyghur medicine (2017) [17]. The TUM diagnostic criteria for CCHS include primary symptoms, secondary symptoms, signs for the tongue and signs for the pulse. The primary symptoms include fever, nasal congestion, nasal discharge and sore throat. The secondary symptoms include cough, headache, thirst, sore limbs and sweating. The signs for the tongue are red tongue and thick yellow tongue coating. The signs for the pulse are hard and rapid pulse. To meet the diagnosis of CCHS, patients should have at least two of the primary symptoms in which fever is essential, and at least two of the secondary symptoms, as well as the TCM signs for the tongue and pulse.

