### Statistical analysis

The independent statistician will conduct the data analysis using SAS 9.4 software (SAS, Cary, NC, USA), in accordance with the statistical analysis plan for this trial. The primary analysis set for efficacy is the full analysis set (FAS) with an intention-to-treat (ITT) principle, in which all patients treated with at least one dose of study drug and who have a clinical observation record should be involved. According to an ITT principle, the last-observation-carried-forward (LOCF) imputation method will be used for missing data. Patients who fulfil the protocol without any major deviations will be included in the per-protocol set (PPS). And all participants who receive at least one dose of the study drug and for whom safety data are available will be included the safety set (SS). Baseline characteristics of all subjects will be analyzed using descriptive statistics for continuous variables and categorical variables. Primary efficacy will be analyzed by comparing outcomes among three groups. Outcomes among three groups will be compared using analysis of variance (ANOVA) and the Bonferroni method. Covariates designated as potential confounders will include age, gender, body mass index (BMI) and duration of symptomatic illness prior to enrollment. Time to fever relief, time to fever clearance and duration of all symptoms will be estimated by the Kaplan-Meier technique and compared by the stratified log-rank test. The improvement of TUM symptoms will be estimated by descriptive analysis for number and proportion of patients achieving clinical recovery. Prespecified subgroup analysis and sensitivity analysis involving covariance analysis will be used to evaluate the primary outcomes according to age and gender. In the multicenter trial, the Cochran-Mantel-Haenszel (CMH) test will be performed to analyze stratified variables. A two-sided *P* value <0.05 is considered as statistically significant.

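### Clinical recovery, set at a 70% fall in the summed symptom score with no fever condition, can include patients who are still febrile, and the only analysis specific to this outcome is a descriptive proportion

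*Protocol article*

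**What the plan says.** The Secondary outcomes section lists change in TUM symptom score. The section of that name builds the score from four primary items ("The primary symptoms are given a graded score (none = 0, mild = 3, moderate = 6, severe = 9") and five secondary items ("the secondary symptoms are given a graded score (none = 0, mild = 1, moderate = 2, severe = 3"). In Table 1 the fever item scores 3 for 37.3–37.9 °C, 6 for 38–38.5 °C and 9 above 38.5 °C. The total is taken at baseline and on day 4, and its change is expressed as PSSR, the fall as a percentage of the baseline total. The section then says that "the improvement of TUM symptoms will be categorized into clinical recovery" and a second class, with one cut between them: "clinical recovery (PSSR ≥ 70%) and invalid (PSSR < 70"%). Nothing else enters the definition.

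Two entry rules bound the baseline total. Inclusion criteria require "fever and body temperature between 38 and 39 °C". Diagnostic criteria say that "patients should have at least two of the primary symptoms in which fever is essential, and at least two of the secondary symptoms".

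For the analysis, the Statistical analysis section says: "The improvement of TUM symptoms will be estimated by descriptive analysis for number and proportion of patients achieving clinical recovery". The same section has a general sentence that compares outcomes among the three groups by ANOVA with Bonferroni, placed directly after a sentence on primary efficacy. It assigns time to fever relief, time to fever clearance and duration of all symptoms to Kaplan-Meier and a stratified log-rank test.

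**The concern.** Fever is essential to the diagnosis and supplies the primary outcome. A category named clinical recovery will be read as meaning that the illness, fever included, is over. A cut on the percentage fall in a sum does not ensure that: a large enough fall in the other items can offset a fever that has not moved, or has risen. The number of residual points allowed also grows with the baseline total, so the same day-4 state can be recovery for one patient and invalid for another.

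The second issue is how the outcome is used. Its name is a change in a graded score, but the one sentence that deals with it specifically describes the proportion above the cut. If that sentence is the whole analysis, the symptom score of a dose-finding trial yields neither an estimated difference between arms nor an interval.

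**Working it through.** The article reports no figure for this outcome that can be reproduced; its sample size concerns the primary outcome and plays no part here. The check uses only Table 1, the 70% cut and the entry rules.

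**Range of the baseline score**
- Maximum: 4 × 9 + 5 × 3 = 51.
- Minimum at entry: fever at 38 °C or more scores at least 6; one further primary symptom at least 3; two secondary symptoms at least 1 each. 6 + 3 + 1 + 1 = 11.

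**Residual score that still counts as recovery**

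PSSR = (B − A)/B, with B the baseline and A the day-4 total. PSSR ≥ 70% is the same as A ≤ 0.3 × B, or B ≥ A/0.3.

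**Fever as the only remaining symptom on day 4**

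| Day-4 temperature | Score A | Smallest B = A/0.3 | PSSR at that B |
|---|---|---|---|
| 37.3–37.9 °C | 3 | 10 | 7/10 = 70.0% |
| 38–38.5 °C | 6 | 20 | 14/20 = 70.0% |
| above 38.5 °C | 9 | 30 | 21/30 = 70.0% |

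- The smallest B in the first row lies below the lowest eligible baseline of 11, where PSSR = (11 − 3)/11 = 72.7%. So every eligible patient whose other symptoms clear is classed as recovered with 37.3–37.9 °C remaining. The section Time to fever clearance requires a temperature below 37.2 °C, sustained for 24 h.
- A baseline of 30 is not an extreme profile: fever 9, the three other primary symptoms at 6 each (18) and secondary items totalling 3 give 9 + 18 + 3 = 30.
- Fever may even worsen. With every item moderate, the baseline is 4 × 6 + 5 × 2 = 34. If fever rises from score 6 to 9 and the rest clears, PSSR = (34 − 9)/34 = 73.5%, which is recovery.
- From a baseline of 37, a patient can still show the minimum entry symptoms on day 4 (total 11) and be recovered: (37 − 11)/37 = 70.3%.

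**Dependence on baseline**
- At B = 11 the largest residual total that passes is 3 (0.3 × 11 = 3.3). At B = 51 it is 15 (0.3 × 51 = 15.3; 36/51 = 70.6%). That residual exceeds another patient's whole entry score of 11.
- A patient who starts at 11 and is afebrile on day 4 with 4 points of secondary symptoms has PSSR = 7/11 = 63.6% and is invalid. A patient who starts at 30 and is still above 38.5 °C is recovered.

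**Reach**

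Of 127,008 score profiles that satisfy the entry rules, 57,540 (45%) total at least 30. This counts possible profiles; it is not an estimate of how many patients are affected.

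**The case against.** The strongest reply is that residual fever cannot be hidden in this trial. Fever relief is the primary outcome, fever clearance has its own definition, and duration of all symptoms ends only when every symptom has gone. The last two are compared by log-rank. That is right, and it limits the harm to one secondary category. It does not repair the label: the same patient can be reported as clinically recovered in one table and as not fever-cleared in another. The extreme case also needs a high baseline, fever above 38.5 °C on day 4 and almost everything else resolved, and the article gives nothing from which its frequency could be estimated.

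A reader might go further and infer that the score is not compared between arms at all. The text does not support that. PSSR is kept as a continuous measure, and the general ANOVA and Bonferroni sentence can be read to cover it, although its position after primary efficacy leaves this open. A statistical analysis plan is referred to but not shown, so the absence of a named test for PSSR is not by itself a fault. What can be criticised is the one specific analysis that is stated.

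A reader might also put a figure on the information lost by the cut, for instance the textbook efficiency of a median split of a normal outcome. PSSR is capped at 100%, may be skewed in a self-limiting illness, and has an unknown distribution around 70%, so no such figure follows. Nor can it be said that the doses could not be separated on symptoms, since duration of all symptoms is compared separately.

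**Conclusion.** The point holds for the definition and, in a limited form, for the analysis. As written, clinical recovery is compatible with fever above 38.5 °C from a baseline of 30, with 38–38.5 °C from 20, and with 37.3–37.9 °C from any eligible baseline, provided the other symptoms clear. These thresholds follow exactly from Table 1, the 70% cut and the entry criteria, and need no assumption about the data. The number of patients concerned is unknown.

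On the analysis, the only statement specific to this outcome is a descriptive number and proportion of a category that depends on baseline severity. Whether PSSR itself is to be compared is unclear from the article.

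This is a secondary outcome, and the primary result is not affected. It is worth correcting because the label is likely to be quoted and the correction is cheap.

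**What to change.** 1. **Definition.** Either call the category response, or add a fever score of 0 on day 4 to the outcome definition of clinical recovery. If the second is chosen, state how it relates to fever clearance: Table 1 implies that score 0 means below 37.3 °C at one assessment, whereas clearance is below 37.2 °C sustained for 24 h.
2. **Main analysis of this secondary outcome.** Compare the day-4 cumulative score between arms with a model containing arm, baseline score and centre, and report differences with 95% confidence intervals. Name in advance a fallback, such as a rank-based or ordinal model, in case many day-4 scores are zero.
3. **Supportive analysis.** Keep the proportion, with a comparison stratified by centre; the CMH test already mentioned in the Statistical analysis section would serve.

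No new data are needed, as both scores are already collected. There are two costs. The reported recovery rate will be slightly lower if the fever condition is added. The change also needs a documented amendment while recruitment is under way (Trial status): under Quality control it requires a justification and approval by the sponsor, the primary investigator in each unit and the statisticians, then presentation to the ethics committee and, if required, the SFDA. It should be settled before unblinding.

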### Safety assessment

Safety assessment, including physical examination and laboratory tests, will be performed at baseline and the fourth day. Physical examination includes vital signs (temperature, respiration, heart rate and blood pressure) and conventional examination (chest, abdomen and nervous system, etc.). Laboratory tests include routine blood test, urine analysis, stool test, measurement of blood electrolytes, liver function test (ALT, AST, alkaline phosphatase (ALP), total bilirubin (TBil) and gamma-glutamyl transpeptidase (GGT)) and renal function test (blood urea nitrogen (BUN), serum creatinine, microalbuminuria, urinary nag enzyme and serum cystatin C). In addition, before treatment, all patients are required to undergo a chest x-ray and electrocardiogram, and female patients of reproductive age are required to take a urinary pregnancy test.

All adverse events (AEs) should be truly recorded in detail on the adverse event form (AEF) and followed up to completion. The patient experiencing an AE will be treated appropriately until recovery from it. A serious AE (SAE) is defined as an adverse event resulting in death, a life-threatening event, an illness requiring hospitalization or severe disability, and it should be recorded and reported to the Principal Investigator, SFDA, ethics committee and the Sponsor within 24 h.

### Quality control

As the monitoring center, Beijing QiHuang Clinical Drug Research Center is in charge of monitoring implementation of the trial protocol, the CRF data and the safety of the participants, as well as contacting and coordinating the various units. The center will assign the Clinical Research Associate (CRA) to regularly review the CRFs and monitor the row data every week. The CRA is blind to trial assignment. Monitoring results should be presented to the Principal Investigator in each site. The Principal Investigator will be responsible for the implementation of the trial, which should be following the standard operation procedure (SOP) for quality assurance and quality control. Any protocol modification should be documented with appropriate justification and approved by the Sponsor, primary investigator in each unit and statisticians. Then the final version should be presented to the Ethics Committee, and the SFDA if required.

### Sample size calculation

Using “One-Way Analysis of Variance F-Tests using Effect Size” in PASS (version 15.0.5), we estimate the sample size with a significance level of 0.05. To our knowledge, no previous study has reported the effective size related to the time to fever relief in our target population (patients with common cold). Thus, we used η2 as an alternative measure of effect size, calculated by:

σm^2^ / (σm^2^ + σ^2^)

to estimate the sample size [21–23]. Generally, the effect size can be defined as follows: η^2^ = 0.0099 ≈ 0.01 is a small effect; η^2^ = 0.0588 ≈ 0.06 is a medium effect and η^2^ = 0.1379 ≈ 0.14 is a large effect [21–23]. In the study, we would like to determine the sample size required to detect a medium effect when the power is 0.90. Therefore, a total sample of 204 subjects (68 in each group) would be required. Assuming an overall 15% drop-out rate, 80 subjects should be recruited in each group. Finally, the total sample size is determined to be 240 patients.

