The Binafuxi is an Uighur herbal medicine prescription and derived from ancient books on Uighur medicine, including *Mahzinul Murakkibat* (Uighur Combination Medicine) and *Karabadin Azam*. It has been used for treating the CCHS for more than 300 years. The prescription is mainly composed of tianshanjincai (*Viola tianshanica Maxim*), heguotenggen (roots of *Operculina turpethum*), gancaojingao (extractum Glycyrrhizae), meiguihua (*Flos rosae rugosae*), sikamoniyazhi (*Resina scammoniae*) and alihong (*Sclerotium fomitis officinalis*). Binafuxi granules are based on the Binafuxi prescription and have been approved by the State Food and Drug Administration of China (SFDA) for a clinical trial (approval number 2014 L01342). Unpublished pharmacologic experiments have demonstrated that Binafuxi granules relieve fever, alleviate cough and sweating and reduce inflammation. The data showed that Binafuxi granules can significantly reduce endotoxin-induced fever in rabbits administered clinical equivalent doses (0.52 g/kg) of Binafuxi granules. Additionally, there was no chronic toxicity found in rats administered different doses of Binafuxi granules (30, 15 and 7.5 times the normal dose) for 1 month except for some cases of diarrhea that occurred in the group receiving 30 times the normal dose.

Since ancient times, many patients have benefited from TUM treatment of the common cold. However, to our knowledge there have been no high-quality clinical studies of the use of TUM in treating the common cold. In conformity with the Drug Administration Law of the People’s Republic of China and good clinical practice (GCP) issued by the SFDA, we designed this randomized clinical trial to evaluate the efficacy and safety of Binafuxi granules in patients with CCHS and to detect the optimal therapeutic dosage.

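### The stated 90% power is correct for the overall three-group F-test but does not carry over to the pairwise comparisons needed for efficacy and dose choice; closed testing would recover part of the gap at no cost in patients

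*Protocol article*

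**What the plan says.** Under Sample size calculation, the protocol article uses the PASS procedure "One-Way Analysis of Variance F-Tests using Effect Size" and says "we estimate the sample size with a significance level of 0.05". The effect is generic: "η^2^ = 0.0588 ≈ 0.06 is a medium effect". The target is stated as "we would like to determine the sample size required to detect a medium effect when the power is 0.90". The result is 68 per group (204 in total), raised to 80 per group (240) for 15% drop-out. No group means, standard deviation, pattern of means or pairwise power is given.

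Under Statistical analysis, "Outcomes among three groups will be compared using analysis of variance (ANOVA) and the Bonferroni method", and "A two-sided *P* value <0.05 is considered as statistically significant". The number of Bonferroni comparisons is not stated, nor whether they follow only a significant F-test. The same section also names a stratified log-rank test for time to fever relief, the primary outcome.

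The Background section gives the aims as evaluating efficacy and safety and "to detect the optimal therapeutic dosage". The closing paragraph of the Discussion adds that the trial may help choose the dose for phase III.

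**The concern.** A significant F-test says only that the three means are not all equal. It does not say that either dose differs from placebo, or that one dose does better than the other. Those answers come from pairwise comparisons, which the plan makes by Bonferroni and for which it states no power. A reader who takes the 0.90 as the chance of answering the efficacy and dose questions will be too optimistic, by an amount that depends on how the means are spread.

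The choice of Bonferroni adds to the gap. With exactly three groups, a procedure that starts from the overall test already planned gives more power for every pair at the same family-wise error rate.

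**Working it through.** **Inputs.** From the article: three equal groups, α = 0.05 two-sided, η² = 0.0588 rounded to 0.06, 68 evaluable per group. Assumed, because the article does not say: all three pairs tested, each at 0.05/3 = 0.0167, and the patterns of means below.

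**1. The plan's own figure.** The noncentrality is λ = N·η²/(1 − η²) = 204 × 0.06/0.94 = 13.02, with 2 and 201 degrees of freedom. Power is 0.904 at 68 per group and 0.8996 at 67, so 68 is the smallest size that reaches 0.90. With η² = 0.0588, 68 per group gives 0.898. Drop-out: 68/0.85 = 80. The stated size reproduces.

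**2. From η² to pairwise differences.** f² = σm²/σ² = 0.06/0.94 = 0.0638, so f = 0.2526.
- Equally spaced means (−δ, 0, δ): σm² = 2δ²/3, so δ = f·√1.5 = 0.309 SD. Adjacent pairs differ by d = 0.309 and high vs placebo by d = 0.619.
- One group differing from two equal ones by D: σm² = 2D²/9, so D = 3f/√2 = 0.536 SD.

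For a fixed σm², the largest difference between any two of three means arises when the third lies midway. So d = 0.619 is the maximum for any pair.

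**3. Pairwise power.** Noncentral t with pooled error (201 df) and noncentrality d·√(n/2), where √34 = 5.831:

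| Contrast | d | Noncentrality | 0.05/3 each | 0.025 each | Closed testing |
|---|---|---|---|---|---|
| High vs placebo, equal spacing | 0.619 | 3.61 | 0.883 | 0.911 | 0.90 |
| Adjacent pair, equal spacing | 0.309 | 1.80 | 0.273 | 0.327 | 0.43 |
| True difference, one group differs | 0.536 | 3.13 | 0.761 | 0.806 | 0.85 |

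The 0.025 column applies if Bonferroni covers only the two dose-vs-placebo tests. High vs low is then outside the family.

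**4. Sensitivity.** With η² = 0.0588, the 0.05/3 figures are 0.875, 0.267 and 0.750. If all 80 per group are evaluable at η² = 0.06, they are 0.93, 0.33 and 0.83.

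**5. Closed testing with three groups.** If the three means are not all equal, at most one pairwise null hypothesis can be true. Testing each pair at 0.05 only after the overall test rejects at 0.05 therefore holds family-wise error at 0.05. In simulation the error was 5.05% when all means were equal and 5.02% when only one group differed. Ungated Bonferroni at 0.05/3 gave 4.4% and 1.7%. The closed-testing powers in the table come from the same simulation (200,000 or more replicates). The argument is special to three groups and does not extend to four or more.

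**6. Showing at least one dose different from placebo.** Simulated power at η² = 0.06 and 68 per group:

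| Pattern | Bonferroni, 0.05/3 | Closed testing |
|---|---|---|
| Equal spacing | 0.89 | 0.90 |
| Both doses equal | 0.89 | 0.90 |
| Only the high dose works | 0.77 | 0.86 |

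**The case against.** The strongest reply is that nothing is misstated. The article names the F-test it sized, and 0.90 is right for that test. This stands: the point is about what the figure covers. Pairwise power could also be left to the full protocol. But the article itself states the 0.90, the Bonferroni method and the dose-finding aim, and these do not line up.

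A reader might infer that the decisive comparisons have 27% to 88% power as a matter of fact. The document does not support that. It fixes neither the pattern of means nor the number of comparisons. The 0.88 is a ceiling only for three-way Bonferroni at 68 per group and η² = 0.06. The 0.27 is not a floor, because a low dose closer to placebo would do worse. With two comparisons the high vs placebo figure reaches 0.91.

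A reader might also infer that Bonferroni throws power away for nothing. That goes too far. Bonferroni is valid, needs no preceding overall test, and has simultaneous confidence intervals that match its tests; closed testing has no simple equivalent. For showing that at least one dose differs from placebo, the gain is small unless only the high dose works.

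It is also fair to say that a phase II trial need not have high power for high vs low. The article does not make the phase III dose depend on a significant result for that contrast.

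**Conclusion.** The point holds as a matter of scope and efficiency; it is not an arithmetic error. The 0.90 belongs to the overall test. Under three-way Bonferroni at the planning values, no pair reaches it. The shortfall is slight for the largest possible contrast (0.88), moderate when one group stands apart (0.76), and severe for adjacent groups with equally spaced means (0.27). Bringing that last contrast to 90% power under three-way Bonferroni would take 284 evaluable per group, against 68 planned.

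Closed testing is a real improvement for every pair, but it does not cure the dose-vs-dose problem, which stays near 0.43 with equal spacing. All the power figures depend on the assumed patterns and number of comparisons, and on the ANOVA route that the article sizes. They do not describe the stratified log-rank test, should that be the primary analysis.

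**What to change.** 1. Under Sample size calculation, state that 0.90 is the power of the overall three-group test. Add the pairwise power, with the assumed patterns of means and the number of comparisons.
2. Under Statistical analysis, for whichever test is chosen as primary, replace Bonferroni by closed testing: the overall three-group test at 0.05, then high vs placebo, low vs placebo and high vs low each at 0.05, only if the overall test is significant.
3. Report all pairwise estimates with confidence intervals at a stated level, for example unadjusted 95%, labelled as unadjusted.
4. Acknowledge that high vs low remains underpowered, and say that dose choice will rest on the estimates and their intervals and will not require a significant high-vs-low test.

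The cost is wording, a less flattering statement of power, and the loss of simultaneous intervals that match the tests. No patients are added and family-wise error stays at 0.05.
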